
## Objectives {7}

The overall goal of UPlusE is to increase the utilization of treatment and counselling services for mothers and fathers experiencing perinatal depression, psychosocial distress, or impaired bonding preceded by a low-threshold screening for these conditions. Within UPlusE, the term psychosocial stress encompasses both psychosocial stress and impaired bonding. The main research question of the UPlusE project is: can the utilization of any support services by parents with psychological or psychosocial issues be improved through the low-threshold intervention? The working hypothesis is: there is a significantly higher utilization of support services in the intervention group between enrolment in the project and the U6 checkup (child’s age of 10–12 months) compared to the control group.

Additional secondary research questions:For parents positively screened for peripartum depression or psychosocial distress (in the following meant as psychosocial distress and impaired bonding):aWhat mental health services are utilized? What is the proportion of medication-based therapies? How quickly do they receive treatment?bHow frequently do various forms of child regulatory problems occur in this group?cDo child regulatory problems occur with varying frequency in families with different stress profiles (mental illness/psychosocial burdens)?

Sensitivity analyses will investigate the following questions:iv.Is the proportion of parents experiencing an improvement in depressive symptom severity higher when utilizing mental health services?v.Is the proportion of parents with an unaffected parent–child relationship higher when utilizing mental health services?vi.Do child regulatory problems occur less frequently in parents utilizing mental health services?

2.Comparison between intervention and control groups at the time of U6 (child’s age of 10–12 months) to answer the following questions:aIs the proportion of parents without depressive symptoms greater in the intervention group?bIs the proportion of parents with an improvement in depressive symptom severity higher in the intervention group?cIs the proportion of parents with an unaffected parent-child relationship higher in the intervention group?dIs the proportion of parents with an improvement in parent-child relationship higher in the intervention group?eIs the proportion of parents with psychosocial burdens smaller in the intervention group?fIs the proportion of children with regulatory problems in areas of crying, sleeping, and feeding smaller in the intervention group?3.For all groups (differentiated by positively and negatively screened parents):aDepressive symptoms, psychosocial burden, parent–child relationship, and child regulation: what is the trajectory of impairment values in different paediatric examinations?bDo child regulatory problems occur more frequently in children of positively screened parents than in children of negatively screened parents?cDo parents feel stigmatized by the screening or the intervention?dWhat healthcare services are utilized in addition to mental health services?eWhat are the healthcare system costs in the first year after birth?fWhat is the acceptance among participating parents for screening and intervention?gHow long is the waiting time until appointments for support services?

Questions at the level of participating practices:h.How well is the screening and intervention (counselling parents with mental health/psychosocial issues and encouraging them to utilize the services of mental health practitioners or support services) accepted among paediatricians and gynaecologists? Where are the potential barriers?i.Do paediatricians and gynaecologists perceive the offered training as helpful and meaningful?

Additionally, as secondary outcomes experiences of violence and birth experiences (fulfilling–traumatic) will be evaluated.

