**Methods:**

UPlusE is a prospective, cluster-randomized controlled trial conducted in an outpatient setting. Obstetric and paediatric practices will be randomized into an intervention and control group (1:1 ratio). Practices and enrolling patients will be required to use specific smartphone apps (practice apps) for interaction. The screening will occur with the apps at each paediatric checkup up to the child’s age of 12 months, using the Edinburgh Postnatal Depression Scale (EPDS), KID-PROTEKT questionnaire, and the scale 1 (impaired bonding) of the Postpartum Bonding Questionnaire (PBQ-1). The goal is to screen 10,000 patients across Germany. Gynaecologists and paediatricians will receive certified training on peripartum depression. Participants in the intervention group with scores above cut-offs (EPDS ≥ 10, KID-PROTEKT ≥ 1, PBQ-1 ≥ 12) will receive counselling through their treating gynaecologists/paediatricians and will be provided with regional addresses for psychiatrists, psychotherapists, and “Frühe Hilfen” (early prevention) as well as family counselling centres, depending on symptom severity. At each screening, participants will be asked whether they sought support, where, and with whom (utilization). Utilization is the primary outcome.

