#### Exclusion criteria

Exclusion criteria include lack of capacity to give consent or an inability to complete the questionnaires in the app (no smartphone, insufficient language, or reading skills). This study thus excludes individuals who cannot operate a smartphone and those who do not speak sufficient German. Many people who do not yet have a sufficient command of the German language use translation programs on their smartphones. If pregnant individuals/parents understand the informed consent and questionnaires adequately with the help of translation programs, they can naturally be included.

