### Relevant concomitant care permitted or prohibited during the trial {11d}

All participants will receive treatment as usual in addition to the study intervention. There are no treatments or interventions that would be prohibited during the study.

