### Outcomes {12}

The primary and secondary endpoints, as well as the parameters of the process evaluation, are presented in Table 1 along with the time points for assessment and measurement methods.

**Table 1 Tab1:** Primary and secondary outcomes UPlusE evaluation

Primary endpoint	Measurement	Time points	Methods
Utilization of services from mental health practitioners/"Early Prevention"	Project-specific questionnaire	From inclusion to U6 checkup	Apps ‘My Paediatric Practice’, ‘My Gynaecology Practice’, all participating parents
Secondary endpoints			
Depression/severity of depression	EPDS (Edinburgh Postnatal Depression Scale)	From inclusion to U6 checkup	Apps (as above), all participating parents
Parent–child bonding	PBQ (Postpartum Bonding Questionnaire)	From inclusion to U6 checkup (child's age of 10–12 months)	Apps (as above), all participating parents
Psychosocial burden	KID-PROTEKT questionnaire	From inclusion to U6 checkup (child’s age of 10–12 months)	Apps (as above), all participating parents
Child regulation	Extended SFS questionnaire	From inclusion to U6 checkup (child’s age of 10–12 months)	Apps (as above), all participating parents
Stigmatization	Project-specific questionnaire	Inclusion and U6 checkup (child’s age of 10–12 months)	Apps (as above), all participating parents
Process evaluation, participant acceptance/satisfaction	Project-specific questionnaire	At U6 checkup (child’s age of 10–12 months)	Apps (as above), parents in the intervention group
Process evaluation, acceptance/satisfaction of participating practices	Project-specific questionnaire	After completion of implementation phase (months 33–35)	Apps (as above), all participating gynaecological and paediatric practices
Process evaluation, acceptance/satisfaction of mental health practitioners/ ‘Early Prevention’	Project-specific questionnaire	After completion of implementation phase (months 33–35)	All involved mental health practitioners/ ‘Early Prevention’ services
Utilization of services in the healthcare system	Analysis of data from the participating health insurance funds	After completion of implementation phase	Data from all participating parents and children
Healthcare system costs in the first year after childbirth	Analysis of data from the participating health insurance funds	After completion of implementation phase	Data from all participating parents and children

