‘quite often’, ‘sometimes’, ‘rarely’, and ‘never’) [27].5.Questionnaire on Crying, Feeding, and Sleeping (SFS):For measuring infant regulatory disorders, the extended SFS questionnaire will be used, comprising 37 items about infant crying, sleeping, and eating behaviour [28]. Total mean scores above 1.84 (crying and sleeping) or above 1.27 (feeding scale) indicate regulatory problems. Six items based on DC: 0–5 (classification system for the diagnosis of mental disorders in infants, toddlers, and preschool children) will be used for further differentiation and clinical classification of symptoms related to excessive crying, sleep disorders, and early childhood feeding disorders.6.Questionnaire on treatment/counselling utilization:Utilization of treatment for mental health issues and counselling for psycho-social stress and parent-child bonding issues will be systematically captured via a project-specific questionnaire in the practice apps ‘My Gynaecology Practice’ and ‘My Paediatric Practice’ through self-report by the participants. The questionnaire assesses information about whether treatment/counselling has been sought. If utilization has occurred since the previous assessment, details such as the institution visited (pregnancy counselling centre, child protection coordination centres, ‘Early Prevention’ services, specialized outpatient clinic, psychiatrist/psychosomatics/psychotherapist, general practitioner, other), the motivating factor, and the referrer will be collected. As of our knowledge, specifically fitting standardized, validated, and publicly published questionnaires for this purpose are currently not available.7.Process analysis questionnaireTo identify technical and organizational barriers as well as facilitating factors for the implementation of the care model, a process evaluation will be conducted. This involves surveying all participating practices, mental health practitioners, and counselling services. Except for mental health practitioners and ‘Early Prevention’, the survey will be conducted using project-specific questionnaires via the practice apps ‘My Gynaecology Practice’ or ‘My Paediatric Practice’. Mental health practitioners and ‘Early Prevention’ services cannot be reached through the practice apps: for the process evaluation, these recipients will be invited to participate in the survey via email by the responsible contact persons from the study team. The survey will use a digital form. The questionnaires for process evaluation will be designed by the Institute for Community Medicine, University Medicine Greifswald, and will cover aspects such as:The number of participating practices, mental health practitioners, and ‘Early Prevention’ services.Their reasons for participation.The feasibility of implementing the intervention in their respective settings.Acceptance of the intervention.Perceived technical and/or organizational barriers or gaps in the implementation of the intervention.Benefits perceived by the involved practices, mental health practitioners, and ‘Early Prevention’ services due to the intervention,Factors promoting the implementation of the care model.

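### The primary endpoint does not separate support started after enrolment from care already under way, and current care is not a named adjustment variable

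*Protocol article*

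**What the plan says.** The working hypothesis in Objectives {7} is that parents in the intervention arm make more use of support "between enrolment in the project and the U6 checkup", and the main research question asks "can the utilization of any support services by parents with psychological or psychosocial issues be improved through the low-threshold intervention". Table 1 under Outcomes {12} lists the primary endpoint as "Utilization of services from mental health practitioners/'Early Prevention", with a window from inclusion to U6. Neither place limits the endpoint to support begun after enrolment or after a positive screen.

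Parents already in treatment may enter. The section on exclusions reads "Exclusion criteria include lack of capacity to give consent or an inability to complete the questionnaires in the app" and does not mention current care. Section {11d} adds "There are no treatments or interventions that would be prohibited during the study".

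On measurement, the Abstract says "At each screening, participants will be asked whether they sought support, where, and with whom (utilization". Section {18a}, item 6, collects details of the service "If utilization has occurred since the previous assessment". The socio-demographic questionnaire in {18a} records a past history of mental health problems, but current care is not named.

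Section {20a} adjusts for covariates only if the arms turn out to differ structurally. Its list of variables is given as examples, and service use at enrolment is not one of them.

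Sample size {14} assumes 15% use in the control group and 25% in the intervention group. The 15% is described as the proportion of all parents who use any mental health services. The section derives 500 parents before, and 1078 screen-positive parents after, allowance for clustering and dropout.

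**The concern.** The trial's rationale is that affected parents go unrecognized and untreated, and that screening with counselling will bring more of them into care. A parent who is already in care at enrolment cannot be moved into care by the intervention. If that parent reports continued use, the parent is an event whichever arm the practice is in.

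Two things follow. First, such parents add events equally to both arms and shrink the observable difference. Second, their share need not be equal. Practices are randomized once their participation is confirmed ({16a}), the same practices recruit the parents ({26a}), and nobody there is blinded ({17a}). A practice that knows its allocation may enrol a different mix of parents, and with clusters an imbalance can also arise by chance. An imbalance in existing users feeds directly into the primary estimate, and the plan does not name the variable that would correct it.

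**Working it through.** **Inputs.** From Sample size {14}: 15% v 25%, power 0.80, 500 in total, design effect 1.725 (taken as given here), 20% dropout, 1078 screen-positive parents. From {20a}: two-sided alpha 0.05. The share q of screen-positive parents who are already in care and report continued use is not in the documents. It is assumed to be 3%, 5% or 8%.

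**Step 1: reproduce the plan's figure.** With the pooled two-proportion formula without continuity correction,
n per arm = [1.96·√(2·0.20·0.80) + 0.8416·√(0.15·0.85 + 0.25·0.75)]² / 0.10² = 250,
so 500 in total, as stated. Then 500 × 1.725 / 0.80 = 1078. In reverse, 1078 × 0.80 / 1.725 / 2 = 250 effective parents per arm, with power 0.800.

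**Step 2: dilution.** Let r be the rate of newly started support among parents not in care. Then
observed rate = q + (1 − q)·r,
and with q equal in both arms,
observed difference = (1 − q) × difference among parents not in care.

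**Step 3: planned rates read as total use.** This is the natural reading of {14}. Solving for new uptake, r = (p − q)/(1 − q). Power for new uptake uses 250·(1 − q) effective parents per arm.

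| q (assumed) | new uptake, control v intervention | difference, points | power, any use | power, new uptake |
|---|---|---|---|---|
| 3% | 12.4% v 22.7% | 10.3 | 0.80 | 0.850 |
| 5% | 10.5% v 21.1% | 10.5 | 0.80 | 0.885 |
| 8% | 7.6% v 18.5% | 10.9 | 0.80 | 0.936 |

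The any-use comparison keeps its 0.80. What changes is the effect needed among parents who can still respond, which is slightly above 10 points.

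**Step 4: imbalance.** If q is higher in one arm by a small amount δ, that arm's observed rate rises by δ·(1 − r). At q = 5%, the factor is 1 − 0.105 = 0.895 if the excess is in the control arm and 1 − 0.211 = 0.789 if it is in the intervention arm. An assumed imbalance of 3 points would move the difference by 3 × 0.789 = 2.4 to 3 × 0.895 = 2.7 points, about a quarter of the planned 10.

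**The case against.** The strongest defence is that total use among screen-positive parents is a legitimate estimand for a trial run in routine care, and that nothing in the document contradicts it. That stands, and it is why the primary endpoint need not be replaced.

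A reader might infer that parents in care are automatic successes. The article does not say so. The Abstract asks whether support was sought, and a parent in long-running therapy could answer no. They can count as events, but it is not certain that they will.

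A reader might also infer that the enrolment answer, which can only describe earlier use, is counted as an outcome. The stated window starts at enrolment, so that answer falls outside it. The article simply does not say how the answer will be used.

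A third tempting inference is that the trial is underpowered. If 15% v 25% described only parents not yet in care, adding existing users would give 17.6% v 27.3%, 19.3% v 28.8% or 21.8% v 31.0% at q = 3%, 5% or 8%, with power 0.74, 0.70 or 0.65. But {14} describes the 15% as use among all parents, so this reading is not supported.

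Finally, {21b} plans a check of structural equivalence at baseline, the covariate list in {20a} is open-ended, and {20c} allows inverse probability weighting. These are partial safeguards. They depend on the imbalance being noticed in a variable that is not named, and a covariate chosen after seeing the data is weaker than one fixed beforehand.

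**Conclusion.** The point holds in a limited form. As stated, the endpoint mixes newly started support with care already under way, and the one variable that would separate them is not named for adjustment. If existing users are balanced, the comparison is not biased, but the absolute difference is shrunk by the factor 1 − q. If they are not balanced, each percentage point of imbalance shifts the estimate by about 0.8 to 0.9 points at q = 5%.

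No loss against the planned 80% power is shown. The 85% to 94% figures describe what a new-uptake analysis could gain under an assumed share of 3% to 8%. They are not a cost of the present plan. The size of the problem cannot be fixed further from the document, because the share already in care is not given and nothing shows that an imbalance exists.

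**What to change.** - State that the utilization answer given at the enrolment screening is a baseline variable and is never counted as an outcome.
- Include it as a prespecified covariate in the primary multilevel model, whatever imbalance is observed.
- Prespecify a supporting analysis of newly started support among parents not in care at enrolment.
- Keep any-use as the primary endpoint.

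The covariate corrects for imbalance and removes noise. It does not take continuing users out of the event count, which is what the supporting analysis is for.

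The cost is one extra covariate and one extra analysis. The Abstract places the utilization question at every screening, so the enrolment answer should already be collected. If it does not identify current care, an item would have to be added to the app. Recruitment began on 9 February 2024 (Trial status), so parents already enrolled would lack that item, and the plan would need to say how they are handled.

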Participants from practices in the intervention group will receive the result of the screening and suitable recommendations for support whenever positively screened during the observation period: pregnant individuals enrolled in gynaecologic practices or parents enrolled in paediatric practices who screen positively during their initial contact with UPlusE will promptly receive the recommendations. Pregnant individuals/parents in the intervention group who are initially screened as negative but are subsequently screened as positive during the course will receive the recommendations from that point onward. As screening tools, the Edinburgh Postnatal Depression Scale (EPDS), the KID-PROTEKT questionnaire, and the scale 1 (impaired bonding) of the Postpartum Bonding Questionnaire (PBQ) will serve. The intervention flow is depicted in Fig. 2. For an EPDS score ≥ 13, trained physicians should encourage the affected parents to promptly consult a mental health practitioner in the region as provided through the app. In case of an EPDS score of 10–12, it is recommended that individuals consider seeking assistance from mental health professionals or, alternatively, ‘Early Prevention’ services. In case of a PBQ scale 1, score ≥ 12, and/or KID-PROTEKT questionnaire ≥ 1 and EPDS < 10, physicians encourage the affected individuals to seek support from ‘Early Prevention’ and other counselling services. The relevant regional addresses will be provided to participants of the intervention group through the apps and the UPlusE website (www.upluse.de). If needed, the physician will support them in making contact. Before each U-checkup, questionnaires are sent again via the app, and the utilization of support services is assessed. The app itself does not guide physicians in treatment recommendations but rather replaces paper questionnaires and calculators to make the screening process more efficient and sustainable.

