## Statistical methods

### Statistical methods for primary and secondary outcomes {20a}

The intervention in UPlusE will be scientifically evaluated using a multidimensional approach and various methods (multilevel analyses, process analyses, secondary data analysis) that, in combination, allow for a comprehensive assessment of different aspects of the project.

All data analyses will be conducted using pseudonymized data. After the observation period (U6), the primary and secondary endpoints for parents with psychological and psychosocial issues will be analysed in a group comparison (comparison between the intervention and the control group). Multilevel analyses will be conducted based on the intention-to-treat principle.

Additionally, the trajectory of values and the utilization of services for parents without psychological and psychosocial issues at the time of project inclusion (clinical evaluation) will be descriptively analysed. Quantitative parameters will be analysed using multilevel analyses to correct for cluster randomization. In the case of structural inequality between the intervention and control groups, relevant parameters (such as age, gender, number of pregnancies and births, partnership, socioeconomics—education, occupation, financial situation, severity of depression) will be adjusted for. All tests will be two-tailed with a significance level of alpha = 0.05.

In the analysis, a descriptive evaluation (e.g. symptom severity, child symptoms, service utilization) will be conducted for the group of parents who were positively screened. At the time of U6, a comparison between the intervention and control groups will be performed (e.g. symptom severity, parent–child bonding, child symptoms). Furthermore, across groups, psychosocial stress, depressive symptoms, stigma, and service utilization will be assessed.

The data from the process analysis questionnaires will be analysed descriptively and inferentially.

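### Questions iv–vi compare parents by actual mental health service use, which the protocol ties to EPDS severity in the intervention arm, and no stated adjustment covers that contrast

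*Protocol article*

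**What the plan says.** Protocol article, Objectives {7}, opens the relevant block with "For parents positively screened for peripartum depression or psychosocial distress" and lists three questions there as sensitivity analyses:

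- iv: "Is the proportion of parents experiencing an improvement in depressive symptom severity higher when utilizing mental health services"
- v: "Is the proportion of parents with an unaffected parent–child relationship higher when utilizing mental health services"
- vi: "Do child regulatory problems occur less frequently in parents utilizing mental health services"

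The randomised counterparts are listed separately as 2a–2f. Improvement is not defined for question iv.

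Intervention description {11a} sets the advice by EPDS band. At 13 or more, "trained physicians should encourage the affected parents to promptly consult a mental health practitioner in the region". At 10–12, "it is recommended that individuals consider seeking assistance from mental health professionals or, alternatively" the early prevention services. Below 10, with a positive PBQ-1 or KID-PROTEKT, parents are pointed to early prevention and counselling. Under {11b}, control parents and their doctors see no results before U6, apart from the suicidality and child-risk alerts.

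Statistical methods {20a} names severity of depression as an adjustment variable, under this condition: "In the case of structural inequality between the intervention and control groups, relevant parameters" are adjusted for. Section {20c} adds that inverse probability weighting may become necessary if groups differ significantly at baseline, without saying which groups.

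**The concern.** Service use arises after randomisation, and in the intervention arm the protocol links it to the severity that also predicts all three outcomes. Users will therefore tend to start with higher EPDS scores than non-users. High scores fall back on re-measurement whether or not treatment works, and a parent who enters with EPDS below 10 through another instrument has little room to fall. A change-based answer to iv then favours services by construction. Questions v and vi ask about status, so the more severely affected users will tend to look worse.

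The adjustment in {20a} does not reach this. The randomised arms can be well balanced while users and non-users differ sharply, and then the stated trigger does not fire. At stake is a secondary report in which services appear to improve depression while worsening bonding and child regulation, with neither finding caused by the services. The sensitivity label adds to the risk, because it suggests a check on the randomised result, which these questions do not test.

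**Working it through.** **Inputs from the article.** It gives no figure for iv–vi, so there is none to reproduce. Sample size {14} assumes 15% use in controls and 25% under intervention. With equal numbers of positives per arm, 0.25 / (0.25 + 0.15) = 62.5% of users would come from the steered arm. The pilot in the Discussion found about 10% with EPDS 10 or more, of whom 43.9% (pregnancy) and 46.9% (postpartum) scored above 12.

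**Assumptions.** Zero service effect. EPDS gamma-distributed, 10% at 10 or more and 45% of those at 13 or more. Correlation of first screen with U6 of 0.4, 0.6 or 0.8. Psychosocial positivity 25%. Bonding and regulatory problems modestly correlated with depression at U6. Use in the bands 13+ / 10–12 / below 10 of 40/20/10% (steep) or 30/20/15% (mild), with a flat 25% as check. Two million parents simulated.

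**Gradient in both arms, all positives, users vs non-users (%).**

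| Outcome | r = 0.4 | r = 0.6 | r = 0.8 |
|---|---|---|---|
| iv, drop of 4+ points, steep | 51 vs 32 | 43 vs 25 | 29 vs 16 |
| iv, drop of 4+ points, mild | 42 vs 33 | 35 vs 27 | 23 vs 17 |
| iv, better EPDS band, steep | 48 vs 22 | 42 vs 20 | 32 vs 16 |
| iv, EPDS below 10 at U6, steep | 79 vs 85 | 71 vs 82 | 61 vs 79 |
| v, unaffected bonding, steep | 90.3 vs 91.6 | 88.3 vs 90.9 | 86.5 vs 90.2 |
| vi, regulatory problems, steep | 24.3 vs 22.1 | 26.9 vs 23.2 | 28.9 vs 24.3 |

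The 4-point drop is spuriously higher in users by 6 to 19 points. With flat use the differences are about 0. Stratifying by first-screen EPDS leaves −0.1 to +0.2 points.

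**Check by hand (r = 0.8, 4-point drop).**

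- Band shares: steep use is 16.35% overall and 29.05% among EPDS 10 or more. The share with EPDS 10 or more is (0.1635 − 0.10) / (0.2905 − 0.10) = 0.333. Of these, (0.2905 − 0.20) / 0.20 = 0.4525 are at 13 or more. The shares are therefore 0.151, 0.182 and 0.667.
- Share at 13+ among parents with EPDS 10 or more: users 0.4525 × 0.40 / 0.2905 = 0.623; non-users 0.4525 × 0.60 / 0.7095 = 0.383.
- Drop rates: in that group 44.1% of users and 40.1% of non-users drop. Solving 0.623a + 0.377b = 0.441 and 0.383a + 0.617b = 0.401 gives a = 0.504 (13+) and b = 0.337 (10–12). Below 10: (0.177 − 0.333 × 0.411) / 0.667 = 0.060.
- Both arms, steep. Users: (0.151 × 0.40 × 0.504 + 0.182 × 0.20 × 0.337 + 0.667 × 0.10 × 0.060) / 0.1635 = 28.6%. Non-users, with 0.60, 0.80 and 0.90 in place of the use rates and 0.8365 as divisor: 15.6%. Simulated: 28.7% and 15.8%.

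**Gradient in the intervention arm only**, controls at a flat 15%. Use per band averages the arms.

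- Steep: 0.275, 0.175, 0.125. Users 0.0367 / 0.1568 = 23.4%; non-users 0.1408 / 0.8433 = 16.7%; difference +6.7.
- Mild: 0.225, 0.175, 0.150. Users 0.0339 / 0.1659 = 20.4%; non-users 0.1436 / 0.8341 = 17.2%; difference +3.2.
- At r = 0.4 the both-arm difference is 19 rather than 13 points. Scaling gives 6.7 × 19/13 = 9.8.

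The range is thus about +3 to +10 points, somewhat more for band change.

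**Restricted to EPDS 10 or more** (gradient in both arms). The 4-point drop differs by +2 to +5 points and band change by about −1.5 to +1. EPDS below 10 at U6 still differs by −1 (72.6 vs 73.5) to −7 (38.6 vs 46.0), so restriction alone is not enough.

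**The case against.** The article lists questions, not models. No unadjusted test is specified for iv–vi, the non-user comparator is implied rather than written, and an analysis plan that is not shown may add terms. Severity is already a named covariate and weighting is allowed. Section {20b} describes the sensitivity analyses as per-protocol analyses of positives who sought help, so iv–vi may be meant as that. Trial design {8} already rests the evaluation on intervention versus control.

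Part of this stands. The unseen plan may contain the remedy, and the randomised evaluation is untouched. But the article does fix the contrast and a severity adjustment whose trigger points at the arms. A per-protocol reading also selects on use, so it does not remove the problem.

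Three stronger readings are tempting and not supported:

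- That iv–vi will show benefit even if services do nothing. This fits only a change-based iv among all positives; v and vi lean the other way, and iv reverses under another reasonable definition.
- That the protocol creates the gradient throughout. Score-based advice is confined to the intervention arm; in controls, self-selection by severity is plausible but is not something the protocol does.
- That a false-positive rate can be stated. The 1078 positives in {14} are tied to depression prevalence of 10–15%, not to positivity on any of three instruments, so no sample size in the article matches this contrast.

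**Conclusion.** The point holds in limited form: as written, iv–vi are confounded by indication. With no service effect, a change-based iv among all positives leans towards benefit by roughly 3 to 10 points if only the intervention arm follows the gradient. If both arms do, it is up to about 20 points (26 for band change at the lowest correlation). The bias is small for change measures among EPDS 10 or more. Under steep use in both arms it turns to −6 to −18 points if improvement means EPDS below 10 at U6. On the same basis users look 1 to 4 points worse on bonding and 2 to 5 points worse on regulatory problems.

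Direction follows from the banded advice and the type of outcome; size rests on assumed use rates and correlations, which the article does not give by severity. The primary outcome and comparisons 2a–2f are unaffected. Severity is minor to moderate.

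**What to change.** For iv–vi, state that the comparison of users with non-users is always stratified by, or adjusted for, EPDS at the first positive screen, whether or not the arms are balanced. Add KID-PROTEKT, PBQ-1 where already answered, and history of mental health problems. For iv, define improvement in advance and restrict to parents with EPDS 10 or more at that screen, keeping the severity adjustment within this group. Write out the comparator. Relabel iv–vi as exploratory associations and say that conclusions about benefit rest on 2a–2f.

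The cost is a few sentences and model terms; under {18a} all variables are already collected. The estimates will be less precise and residual confounding remains, so no causal claim should follow even after adjustment.
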